### Surface-level analysis

Because more than one carious lesion may be included from one child, these lesions will possibly be correlated or clustered. Therefore, an adjustment of the clustering effect will be required. Multilevel logistic regression analysis will be adopted to assess the relative effectiveness of a 25% AgNO_3_ and a 5% NaF varnish with or without fTCP in arresting dentine caries. A two-level model will be used: level 1, tooth surface level, and level 2, subject level. Multilevel logistic regression models with a clustering effect adjustment will be performed to analyze the effect of independent variables on the caries-arresting outcomes at the 12-, 18- and 30-month follow-ups. Besides treatment group assignment, other potential variables, such as demographic characteristics (sex and age), oral hygiene status, oral-health-related behaviors, level of parental education, family income, caries condition (baseline dmfs scores, tooth position, lesion site and presence of plaque on lesion), also will be included in the model as covariates.

The secondary outcome (preventive effect) is the mean of caries increment at the 6-, 12-, 18-, 24- and 30-month examinations. A paired *t* test will be performed to assess the difference in the caries increment between the two groups at all follow-up examinations. Multilevel generalized linear models will be adopted to assess the effect of independent variables on the caries increment between two groups at 12, 18 and 30 months.

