### Objective

The objective of this randomized, double-blind controlled trial is to compare the caries-arresting effectiveness of a 5% NaF varnish with fTCP and that of a 5% NaF without fTCP when applied semi-annually following the application of a 25% AgNO_3_ solution in preschool children over 30 months. The secondary objective is to compare the effectiveness of a 5% NaF varnish with fTCP and that of a 5% NaF without fTCP in preventing dental caries in preschool children over 30 months.

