### Outcome measure

Outcome measures will be collected at baseline and semi-annually thereafter for 30 months. The primary outcome measure of this study is the proportion of soft (active) carious surfaces that become hardened (arrested). Lesion activity will be assessed based on visual and tactile sensation. A lesion will be recorded as active if softness is detected upon gentle probing, and it will be classified as arrested caries if the lesion is hard [19, 24].

The secondary outcome measure is the caries increment or the change in the dmfs score over time, which will be measured by a calibrated dental examiner who is masked to the group assignment. Visual and tactile inspection without x-rays will be adopted.

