### Statistical methods

The collected data will be entered into an Excel file by two persons separately, and the data will be proofread to minimize data-entry error. Data will be analyzed using the software SPSS 24.0 for Windows (SPSS Inc., Chicago, IL, USA). The statistical significance level for all tests will be set at 0.05.

An intra-examiner agreement in the diagnosis of dental caries will be assessed by Cohen’s Kappa statistics. An intention-to-treat analysis will be undertaken. The dropout rates of the two groups will be expected to be similar as the treatment protocols and treatment outcomes (arrested caries with blackening of the lesion) are similar.

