Although clinical trials have demonstrated that SDF is effective in arresting dentine caries in primary teeth, there was a significant increase of new caries development during the trials, as SDF is only applied on the existing cavitated lesions [24, 29]. However, the application of NaF varnish following SDF application at the same visit may increase the risk of fluoride toxicity. It should be noted that SDF is still unavailable in many countries. An alternative to arrest caries using a 5% NaF varnish applied following a 25% AgNO_3_ solution was developed [22]; however, there is a lack of information regarding the preventive effect. Several laboratory studies have shown the anti-caries properties of NaF containing fTCP [12, 14–17], but the clinical efficacy remains unknown. This study will adopt the commercially available product with fTCP, exclusively from 3 M (Clinpro White Varnish), which contains 5% NaF and fTCP less than 5% by weight. The results of the present study will be novel and will provide information regarding the preventive and arresting effect of the application of NaF varnish with/without fTCP following the application of a 25% AgNO_3_ solution in preschool children.

Because the proposed caries management method in this study is simple, noninvasive and low cost, it can be widely recommended and adopted for caries prevention and caries arrest in young children, children with special needs or those living in disadvantaged communities. The results of this study will be beneficial for clinicians and dental health policy-makers when adopting noninvasive approaches to tackle the burden of early childhood caries.

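### The preventive outcome is tested between arms at five visits and modelled again at three of them, each at 0.05, with no rule making the 30-month result or either method decisive

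*Protocol article*

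**What the plan says.** The Objective section has one secondary objective, a comparison of the two varnishes "in preventing dental caries in preschool children over 30 months". The Outcome measure section is less specific about time: "The secondary outcome measure is the caries increment or the change in the dmfs score over time".

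The Surface-level analysis section then spreads the outcome over five visits: "The secondary outcome (preventive effect) is the mean of caries increment at the 6-, 12-, 18-, 24- and 30-month examinations". For the group comparison, a t "test will be performed to assess the difference in the caries increment between the two groups at all follow-up examinations". In addition, multilevel generalized linear models are to "assess the effect of independent variables on the caries increment between two groups at 12, 18 and 30 months".

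On error control there is one sentence, in Statistical methods: "The statistical significance level for all tests will be set at 0.05". The article does not rank the visits, choose between the t test and the model, or mark any of these comparisons as supportive.

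**The concern.** One objective is examined up to eight times: five t tests and three models, each at full alpha. Read as written, a significant difference at any visit, by either method, could be reported as a preventive effect of fTCP. The 5% level applies to each test and not to that conclusion. At 12, 18 and 30 months the t test and the model can also disagree, and nothing says which prevails.

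Prevention is one of the two effects the trial sets out to report: the Discussion says that the results "will provide information regarding the preventive and arresting effect" of the varnishes, and it goes on to recommend the approach for wide use in prevention. A chance finding at one visit would feed directly into that message.

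**Working it through.** **The plan's own figures.** The article computes a sample size for the primary outcome only and states no power or overall error for the secondary outcome. As a check that the primary design is untouched:

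- Two proportions, 70% against 80%, power 90%, two-sided 0.05: 392 surfaces per arm (784) without continuity correction and 412 per arm (824) with it. The article has 820, close to the corrected value.
- Design effect: 1 + (3 − 1) × 0.13 = 1.26, as stated.
- Children: 410 × 1.26 / 3 = 172.2, so 173 per group and 346 in total; 346 / 0.85 = 407.1, so 408. Both as stated.

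**Inputs for the secondary outcome.** From Surface-level analysis: five t tests (6, 12, 18, 24 and 30 months) and three models (12, 18 and 30 months). From Statistical methods: 0.05 per test. Two-sided testing is taken from the sample size section. The correlations are assumptions, because the article gives none. Each t test is treated as a valid 5% comparison of two independent groups; the article's naming of a paired test is a separate matter, not used here.

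**Independence bound.** 1 − 0.95^5 = 0.226, or 4.5 times 0.05. For eight tests, 1 − 0.95^8 = 0.337, which is not realistic because the models reuse the same data at the same visits.

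**Five t tests on cumulative increments.** Change in dmfs is most naturally measured from baseline, so later values contain earlier ones. If 6-month steps have equal variance and correlate r within a child, the test statistics at visits s < t (numbered 1 to 5) correlate √{s[1 + r(t − 1)] / (t[1 + r(s − 1)])}. With r = 0 this is √(s/t): 0.45 between 6 and 30 months, 0.89 between 24 and 30 months. Simulating 1,000,000 multivariate normal draws under no effect, with cut-off 1.96:

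| Step correlation r | At least one p < 0.05 | Multiple of 0.05 |
|---|---|---|
| 0 | 14.2% | 2.8 |
| 0.1 | 13.1% | 2.6 |
| 0.2 | 12.2% | 2.4 |
| 0.3 | 11.4% | 2.3 |
| 0.5 | 9.9% | 2.0 |

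**Five t tests on separate 6-month increments.** With correlation 0 to 0.5 between visits the chance is 22.6% to 18.3% (4.5 to 3.7 times).

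**All eight tests, cumulative increments.** Each model statistic is assumed to correlate 0.80 to 0.95 with the t statistic at the same visit, and across visits by that value times the between-visit correlation. The chance is 19.0% to 16.5% at r = 0 and 13.7% to 11.7% at r = 0.5, or 2.3 to 3.8 times 0.05.

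**Outside these cases.** Adding the models to weakly correlated visits would pass 23%: with equal between-visit correlation 0.3 and t/model correlation 0.95 to 0.85, it is 24.2% to 26.6%. That is not the natural reading of change in dmfs, so it is left out of the headline range.

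**Direction.** Results favouring fTCP are about half of each figure: for the five cumulative tests at r = 0, 7.1% against a nominal 2.5%.

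**The case against.** The strongest reply has four parts.

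- *A hierarchy for a secondary outcome usually sits in the full protocol or analysis plan, which is not shown.* Silence alone would indeed be no finding. But the article is not silent: it fixes the visits, both methods and 0.05 for every test. A hierarchy elsewhere would have to be reconciled with that text.
- *The objective already points to 30 months.* This stands in part. A reader might infer that the article gives no time point at all, and it does give a horizon. What it lacks is a rule that the 30-month result decides, and by which method.
- *The models may be ordinary adjusted analyses rather than further chances of success, and the Discussion promises information rather than proof.* Also fair. Counting only the t tests, the chance is still about 10% to 23%. No sentence says that one significant visit proves prevention; the point is that none prevents that use.
- *The size rests on assumptions, and two-sided figures overstate the risk of a claim for fTCP.* Both are correct. A reader might infer a flat inflation of three to five times. The documents do not support that: they give no correlations, and the five cumulative tests give 2.0 to 2.8 times. The 4.5 end needs visits that are independent.

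**Conclusion.** The point holds at moderate size. With no true difference, at least one two-sided p below 0.05 is expected in roughly 10% to 23% of trials, about 2 to 4.5 times the nominal 5%. On the cumulative reading it is about 10% to 14% for the five t tests, and about 12% to 19% with the three models added at an assumed t/model correlation of 0.80 to 0.95. The upper end of 23% is the independence bound for five tests. For results favouring fTCP, halve each figure and compare it with 2.5%.

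Two stronger conclusions do not follow. The error rate of the primary arrest outcome and the sample size are not affected, since the tests counted here are all of the secondary outcome. Nor do the documents require prevention to be tested only after a significant arrest result: the Objective section states the two aims separately, and such gating is a design choice.

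**What to change.** In Surface-level analysis, name the 30-month between-group difference in caries increment, from the multilevel generalized linear model, as the single comparison that decides the secondary objective at two-sided 0.05. State that the 6-, 12-, 18- and 24-month comparisons and all the t tests are supportive, reported as estimates with 95% confidence intervals and without a claim of effect. Limit the general 0.05 sentence in Statistical methods to match. Making the 30-month test conditional on the primary result is optional.

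This returns the error for a prevention claim to 5% and uses the horizon already in the sponsor's objective. It costs a few sentences and needs no new data or children. Keeping all tests as decisive would instead need a Bonferroni level of 0.05 / 5 = 0.01 for five tests or 0.05 / 8 = 0.00625 for eight. The small downside is that significance at an earlier visit alone could no longer be reported as a demonstrated preventive effect.

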## Methods/design

### Trial design

This is a double-blind, two-armed, parallel-design randomized controlled trial. The Standard Protocol Items: Recommendations for Interventional Trials (SPIRIT) 2013 Statement will be followed in this trial (Additional file 1) [23]. The schedule of this study is presented in Fig. 1.

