### Randomization, treatment allocation and allocation concealment

Participating children with dental caries will be categorized into two strata by the number of carious surfaces they have (one to three or more than three tooth surfaces). The children will be then allocated by a stratified randomization method with a block size of 6 into two groups. The allocation sequence will be generated by a technician who will not be involved in the oral examination and patient allocation. A pile of sealed opaque envelopes with the allocation numbers will be prepared. Those envelopes will be held by a dental assistant in the field. The assistant will know the treatment allocation only when they open the envelope.

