### Interventions

A dentist who is not involved in the assessment of the carious lesions will apply the solution and varnish with a micro-brush on the carious lesion according to the assigned treatment group after the oral examination.

Two intervention groups in this study are as follows:Group A: a 25% AgNO_3_ solution (25% silver nitrate, Gordon Labs, Carson, CA, USA) followed by a 5% NaF varnish (Nupro White Varnish, Dentsply, York, PA, USA),Group B: a 25% AgNO_3_ solution (25% silver nitrate, Gordon Labs, Carson, CA, USA) followed by a 5% NaF varnish with fTCP (Clinpro White Varnish, 3 M, St. Paul, MN, USA).

After applying the solution and varnish on the carious lesion(s) for arrest purposes, the assigned 5% NaF varnish (0.25 ml) will be applied on all tooth surfaces of each child to prevent dental caries according to their assigned treatment group. After the treatment, the children will be instructed not to eat or drink for 30 min. The intervention will be provided every 6 months.

An individual report on the child’ s oral health status will be distributed to the parents or guardians with a note asking them to report to the study dentist if there are any adverse effects on the treated tooth and/or the surrounding gum and mucosa after treatment. A referral letter will be provided to seek the appropriate dental treatment if needed. Parents and teachers will be informed that if the treatment has successfully arrested the carious lesions, yellow and soft carious surfaces will become hard and black in color.

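### The paired t test planned to compare caries increment between the two arms has no pairing to work on in this parallel trial; an independent-samples test should be named instead

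*Protocol article*

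**What the plan says.** The Trial design section describes a "double-blind, two-armed, parallel-design randomized controlled trial". Allocation is at child level: "The children will be then allocated by a stratified randomization method with a block size of 6 into two groups". The strata are one to three versus more than three carious surfaces, and no matching of children across groups is described. Each child receives one varnish over the whole mouth; under Interventions, "the assigned 5% NaF varnish (0.25 ml) will be applied on all tooth surfaces of each child".

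The secondary objective is to compare the two varnishes "in preventing dental caries in preschool children over 30 months". Under Outcome measure, "The secondary outcome measure is the caries increment or the change in the dmfs score over time". The Surface-level analysis section adds that this outcome "is the mean of caries increment at the 6-, 12-, 18-, 24- and 30-month examinations", and then names the test: "A paired *t* test will be performed to assess the difference in the caries increment between the two groups", at all follow-up examinations. Its next sentence plans multilevel generalized linear models for the increment between the two groups, at 12, 18 and 30 months only.

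**The concern.** A paired t test works on the differences within defined pairs. Here the contrast is between arms, and nothing in the design links a child in group A to a child in group B. An analyst who follows the sentence literally must either invent a pairing, in practice the row order of the file, or silently run a different test from the one in the plan.

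At stake is the simple between-group test of the trial's secondary objective at five visits. A p-value that depends on file order cannot be reproduced by a second analyst. Leaving out unpaired children also sits badly with the intention-to-treat analysis promised under Statistical methods.

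**Working it through.** **1. Is there any pairing?** The possible sources, set against the protocol:
- Matched children: none. Stratified blocks of 6 balance the arms but do not form pairs.
- Split-mouth or crossover: none. One assigned varnish goes on all tooth surfaces, in a parallel design.
- Baseline and follow-up of the same child: already used up, because the increment is itself the change in dmfs.

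No valid pairing remains. This conclusion needs no numerical assumption.

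**2. The plan's own numbers.** Sample size and power calculation gives 410 surfaces per group, about 3 surfaces per child, an intraclass correlation of 0.13 and 15% dropout.
- Design effect: 1 + (3 − 1) × 0.13 = 1.26, as stated.
- Children per group: 410 × 1.26 / 3 = 172.2, rounded up to 173, so 346 in total, as stated.
- With dropout: 346 / 0.85 = 407.1, rounded up to 408, or 204 per group, as stated.

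These figures rest on the primary outcome. The protocol gives no power, mean or SD for the caries increment.

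**3. Would the arms even be of equal size?** Assume that each of 204 children per arm is retained independently with probability 0.85.
- Variance of completers per arm: 204 × 0.85 × 0.15 = 26.01, so SD = 5.10.
- P(equal numbers) ≈ 1 / (2 × √π × 5.10) = 0.055. The exact binomial sum is 0.0553.
- Mean absolute difference ≈ √(2 × 26.01) × √(2/π) = 7.21 × 0.798 = 5.75 children.

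So in about 94.5% of trials the paired test could run only after about six children on average, against 173 expected per arm, had been left out of the larger arm.

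**4. Degrees of freedom with 173 completers per arm.** Paired: 173 − 1 = 172. Independent samples: 173 + 173 − 2 = 344. The two-sided 5% critical values are 1.974 and 1.967, so this loss is small.

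**5. Row order (illustration only).** Increments were simulated as negative binomial with dispersion 1 and 173 per arm. The distribution and means are assumptions.
- One data set with assumed means of 3.0 and 2.5: independent-samples p = 0.166. Over 10,000 random pairings, the paired p ran from 0.085 to 0.213.
- Same data, artificial extremes: p below 0.000001 with both arms sorted by outcome, and 0.26 with the arms sorted in opposite directions.
- Type I error over 20,000 null trials with mean 3: 0.0496 for the arbitrarily paired test and 0.0505 for the independent test.
- Control mean 3.0, other arm 3.0 down to 2.0, 10,000 trials each: the two tests disagreed at the 0.05 level in about 0.8% to 2.2% of trials.

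**6. Coverage by visit.**

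| Visit (months) | Paired t test | Multilevel model |
|---|---|---|
| 6 | yes | no |
| 12 | yes | yes |
| 18 | yes | yes |
| 24 | yes | no |
| 30 | yes | yes |

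**The case against.** The strongest reply is that the word is a slip with little consequence. The Subject-level analysis section names an ordinary t test for baseline differences between groups, so the authors evidently know the right tool. The next sentence of the Surface-level analysis section plans a between-group model that covers 30 months, the horizon of the secondary objective. Arbitrary pairing leaves type I error near nominal and rarely changes the decision at 0.05. Most of this stands and limits the severity. It does not rescue the sentence: the stated test has no defined input, it is the only between-group analysis named at 6 and 24 months, and at the other three visits nothing says which of the two analyses governs.

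Three stronger readings are tempting but unsupported:
- A reader might infer that the secondary objective has no sound analysis. The multilevel models at 12, 18 and 30 months show otherwise.
- A reader might infer a raised false-positive rate. That would need a row order related to the outcome, and nothing in the protocol suggests one.
- A reader might take the test as baseline versus follow-up within each arm, so that the arms would be judged by which one is significant. The sentence says between the two groups, and the increment is already the within-child change. Nor does the protocol give an SD from which the effect of that practice could be sized.

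**Conclusion.** The point holds as a misnamed test for the secondary outcome and should be fixed. That no pairing exists follows from the design alone. The consequences are a p-value that depends on row order, the omission of about six children on average (equal arms in only about 5.5% of trials, assuming independent 85% retention of 204 per arm), and 172 instead of 344 degrees of freedom. The row-order figures are illustrative and rest on an assumed distribution. Systematic inflation of type I error is not shown. The primary analysis by multilevel logistic regression and the 408 children are unaffected, which keeps this below the level of a must-fix.

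**What to change.** In the Surface-level analysis section, replace the paired t test with an independent-samples (Welch) t test of the increment between groups at each follow-up examination. Add one sentence stating that the multilevel generalized linear model is the main between-group analysis of the secondary outcome at 30 months. Adjusting that model for the randomisation stratum (one to three versus more than three carious surfaces) is an optional addition.

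The cost is one or two sentences, settled before the data are analysed. No extra data are needed, and no stated number changes.

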### Ethical consideration

Ethics approval was obtained from the Institutional Review Board of The University of Hong Kong/Hospital Authority Hong Kong West Cluster (HKU/HAHKWIRB) (IRB reference number: UW17–176). An information sheet about this study will be distributed to parents or legal guardians, and parental consent will be obtained prior to a child’s participation. Children and their parents/legal guardians maintain their rights to receive dental treatment by other dentists. From our previous experiences in conducting clinical trials [11, 18], most participants did not seek help from other dental personnel. In the present study, a question about the receipt of other dental treatments will be included in the baseline and follow-up questionnaires. Medical record notes of the participants may be checked by responsible individuals from the Faculty of Dentistry, The University of Hong Kong or HKU/HAHKWIRB.

